### Performance assessment

2.4

After collecting baseline data, participants will perform two motor tests as part of Phase 3 of the protocol. The first is the LSPT, which assesses passing accuracy and speed under time pressure in a standardized soccer-specific context. Participants perform 16 passes to designated targets announced in sequence, with performance assessed by total execution time adjusted for penalty points for technical errors (e.g., incorrect passes, errors in the target area, poor ball handling) and bonus points for accurate actions. This scoring protocol has been validated in youth and elite football players (56, 57). The test will be filmed with two cameras for subsequent technical analysis and penalty verification. A schematic representation of the LSPT setup is provided in Figure 2, adapted from Ali et al. (34).

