This methodology combines EEG, head-mounted eye tracking during the LSPT, validated agility assessment with the Y-SART, and subjective fatigue ratings to provide a multimodal characterisation of mental-fatigue responses. Our hypothesis is that, compared to a low-load control condition, a 30 min ST will induce higher subjective fatigue, altered frontal-parietal EEG activity, less efficient visual exploration, and decrements in football-specific performance. If confirmed, these findings will support the use of this protocol as a replicable framework for research and applied monitoring in high-performance football environments.

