#### Technical and motor performance

2.5.3

Technical and motor performance will be assessed using the LSPT and the Y-SART, using Witty SEM indicators (Microgate, Bolzano, Italy). These instruments allow the effects of mental fatigue on technical execution, reactive agility and decision-making processes in a sporting context to be quantified with high temporal precision and reliability.

Comparisons between groups will examine whether the ST induces greater impairments in performance metrics compared to a cognitively neutral task. The LSPT will provide data on total execution time, technical penalties, and adjusted score, while the Y-SART will produce reaction and execution times in response to visual stimuli. These comparisons will elucidate the degree to which mental fatigue affects motor fluency, visuomotor coordination, and accuracy under pressure.

Intra-subject analyses in the experimental group will allow for the detection of performance deterioration caused by the ST. By comparing pre- and post-intervention scores on both the LSPT and Y-SART, this approach will help determine whether mental fatigue results in statistically significant reductions in motor and technical efficiency.

The associations between performance metrics and indicators of fatigue (e.g., VAS, EEG, and ETS) will also be examined to explore whether higher levels of perceived or physiological fatigue correlate with slower and less accurate performance. These relationships may help identify which dimensions of fatigue are most predictive of declines in physical performance.

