##### LSPT

2.5.3.1

In the LSPT, the variables total execution time, technical penalties, and adjusted score will be analysed, indicators that simultaneously integrate motor speed, technical accuracy, and cognitive efficiency under time pressure. This protocol demonstrates high ecological validity and excellent test-retest reliability for assessing technical proficiency and decision-making performance in football (4, 57). Recent evidence shows that mental fatigue leads to an increase in total time and penalty time, indicating that mentally fatigued athletes are more prone to technical errors, such as missing target zones. This decline in performance appears to stem from a shift in attention towards irrelevant stimuli rather than task-relevant stimuli, resulting in poorer technical execution and slower motor fluency (80, 81).

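### LSPT penalties and the adjusted score are human-judged and compared between arms, but the article describes no masking of the scorer to arm

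*Protocol article*

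**What the plan says.** Section 2.4 (Performance assessment) builds the LSPT score as "performance assessed by total execution time adjusted for penalty points for technical errors", with bonuses for accurate actions. Its examples of errors are "incorrect passes, errors in the target area, poor ball handling". It adds that "The test will be filmed with two cameras for subsequent technical analysis and penalty verification".

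Section 2.5.3.1 (LSPT) states that "the variables total execution time, technical penalties, and adjusted score will be analysed". Section 2.5.3 (Technical and motor performance) gives their use: "Comparisons between groups will examine whether the ST induces greater impairments in performance metrics compared to a cognitively neutral task". The Introduction sets the direction; the Stroop arm is expected to show "less efficient visual exploration, and decrements in football-specific performance".

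On sequence, section 2.2 places randomisation after the baseline assessment. Section 2.4 has both motor tests repeated in Phase 5, after the Phase 4 task and in the same session. For the Y-SART, section 2.4 describes automatic time recording.

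No section says whether the person scoring the LSPT live, or the person reviewing the video, knows the arm. None mentions coding or shuffling of clips.

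**The concern.** Whether a touch was poor ball handling, or whether a pass met the target, is a judgement call. If the person making it knows that the player has just done 30 minutes of Stroop rather than read magazines, and the study expects Stroop to impair performance, borderline calls can drift in the expected direction.

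That error would depend on arm, so randomisation does not balance it. Adjusting for the baseline score, or testing change from baseline, does not remove it either, because the error enters with the scoring and not with the player. Baseline clips are not safe by default: they are filmed before allocation, but if the video is reviewed later the arm may be known by then.

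At stake is whether a between-arm difference in penalties or adjusted score reflects fatigue or scoring.

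**Working it through.** **1. The plan's own sample size.** Inputs from section 2.2: repeated-measures ANOVA, 2 groups, m = 2 times, f = 0.25, alpha 0.05, power 80%, N = 34 (17 per group). The pre-post correlation rho is not stated; 0.5 is assumed. For the group-by-time interaction, lambda = f² × N × m / (1 − rho), with 1 and N − 2 degrees of freedom.

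- N = 34: lambda = 0.0625 × 34 × 2 / 0.5 = 8.5, power 0.807.
- N = 32: lambda = 0.0625 × 32 × 2 / 0.5 = 8.0, power 0.781.

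So 34 is reproduced, and 17 per arm is used below. Masking does not change this number.

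**2. Which outcomes are exposed.**

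| Outcome | How obtained | Exposure to scorer judgement |
|---|---|---|
| LSPT technical penalties | Judged errors, verified on video | High |
| LSPT adjusted score | Time plus judged penalties and bonuses | High |
| LSPT total execution time | Timed | Lower |
| Y-SART times | Automatic recording | Little |

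**3. What a scoring shift would do.** The article gives no bias size, so the shift b is assumed and a range is shown. The test is the independent t-test between arms that section 2.6 plans at each time point. With no true effect and n = 17 per arm, the statistic follows a noncentral t with 32 degrees of freedom and noncentrality b × √(n/2) = b × √8.5 = b × 2.915. The error rate is the probability of falling beyond the two-sided 5% critical values.

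| Shift b (SD of analysed score) | Noncentrality | Error rate |
|---|---|---|
| 0 | 0 | 5.0% |
| 0.1 | 0.292 | 5.9% |
| 0.2 | 0.583 | 8.7% |
| 0.3 | 0.875 | 13.6% |
| 0.5 | 1.458 | 29.3% |

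**4. Dependence on scale.** If the shift affects only the post-test and is measured in SDs of the raw score, but change scores are analysed, the SD of change is the raw SD × √(2(1 − rho)). At rho = 0.5 this factor is 1 and the table stands. At rho = 0.8 it is √0.4 = 0.632, and shifts of 0.1, 0.2, 0.3 and 0.5 raw SD give 7.3%, 14.5%, 26.9% and 60.9%.

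**5. Can the clips be masked?** Both arms do the same Phase 5 retest with the same equipment, and the Phase 4 task is finished before filming, so a clip need not show the arm. If the eye-tracking headset is worn only in Phase 5, it would show phase but not arm.

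**The case against.** The strongest objection is that the article is silent and does not say that scorers are unmasked. It is a condensed account, and who scores which clip could stand in a fuller protocol. Two-camera verification is itself a safeguard against live mis-scoring. The first part stands: a reader might infer that scoring is open to arm, and the text does not establish that. The condensation argument is weaker. Masking of outcome assessors is a basic design item. This article reports electrode impedance limits, the component-classification threshold and the number of cameras, and section 2.1 says that internal validity has priority. Video verification improves accuracy, but it does not by itself prevent arm-dependent judgement.

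Four further readings go beyond the text:

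- **The LSPT as the main outcome.** It is the only passing test, but the analyses that the article calls primary are EEG analyses (sections 2.5.1.1, 2.5.1.2 and 2.6).
- **A specific prediction of more penalties.** Section 2.5.3.1 says that "mental fatigue leads to an increase in total time and penalty time", but as a summary of earlier evidence. The protocol's own hypothesis concerns football performance in general.
- **The same staff running Phase 4 and scoring.** No section says who does either.
- **Renaming files as sufficient.** A scorer who saw the player's Phase 4 could recognise the player on video, so the choice of scorer matters as much as the coding.

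It is also fair to object that the shifts in the working are hypothetical. They show how sensitive a trial of this size is; they do not estimate bias in this study.

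**Conclusion.** The concern holds for LSPT technical penalties and the adjusted score. They are judged outcomes, compared between arms under a directional hypothesis, and no masking of the live scorer or the video reviewer is described. It does not extend with the same force to execution time, nor to the Y-SART.

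The size of any bias is unknown. At 17 per arm, even an arm-dependent shift of 0.2 to 0.5 SD of the analysed score would lift the nominal 5% error rate to between about 9% and 29%. That range rests on an assumed shift, no true effect, and an independent t-test on the score in which the shift is expressed.

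This should be settled before data collection. It calls for a change in how scores are produced as well as a sentence of reporting, because the safeguard must be in place when the clips are scored.

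**What to change.** State in section 2.4 that:

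1. LSPT clips from both the baseline and the post-intervention test are saved under random codes.
2. Penalties are scored from the coded clips, in random order, by a member of the existing team who did not attend that participant's Phase 4 and has no access to the allocation.
3. This masked video score, and not any score given live, is the analysed value for technical penalties and the adjusted score.

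The cost is file coding, an order list, a split of duties within the team, and scores that become available only after the session. No additional measurement, visit or participant is needed. A headset worn only in Phase 5 may let the scorer tell phase, which should be acknowledged; it does not reveal arm.

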**Figure 2 F2:**
[figure not shown]
Schematic representation of the LSPT, adapted from Ali et al. (34).

The second physical performance test is the Y-SART, designed to assess agility and reaction time to visual stimuli. Participants start the course from a fixed point and, after an initial start, must react to a visual stimulus provided by the WITTY SEM system, which indicates the need to deviate to the left or right on the Y-SART course. Times are automatically recorded from the start to the finish line, ensuring accurate measurement of reaction and movement speed. A schematic representation of the Y-SART configuration is also provided, in Figure 3, adapted from Yuan et al. (2).

**Figure 3 F3:**
[figure not shown]
Schematic representation of the Y-SART, adapted from Yuan et al. (2).

After completing Phase 3, participants move on to Phase 4, where they perform the cognitive intervention defined by their group assignment, either the ST (experimental group) or a neutral task, such as reading magazines (control group). This is followed by Phase 5, which begins with participants completing the VAS again. Next, both motor tests are repeated, this time with continuous recording by the ETS. Finally, a second EEG recording is performed under the same conditions as in the initial phase, concluding the data collection session.

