To ensure data quality and reproducibility, EEG signals will undergo standardized pre-processing procedures. Data will be processed in MATLAB R2025a (MathWorks, Natick, MA, USA) using EEGLAB v2025. Continuous recordings will be visually inspected to identify gross artifacts or recording instabilities, and non-EEG channels will be removed prior to analysis. Signals will be band-pass filtered between 1 and 45 Hz using a zero-phase finite impulse response (FIR) filter and re-referenced to a common average reference. Artifact correction will be performed using Independent Component Analysis (extended infomax algorithm). Independent components will be automatically classified using the ICLabel plugin integrated in EEGLAB, and components identified as ocular, muscular, cardiac, line-noise, or other non-brain sources with high probability (≥0.90) will be removed prior to signal reconstruction. Channels exhibiting persistent excessive noise throughout the recording will be excluded from analysis. All preprocessing procedures will be applied consistently across participants and experimental conditions to ensure methodological standardization and internal validity.

Oculomotor activity will be recorded with the Pupil Core system (Pupil Labs GmbH, Germany), with sampling at 200 Hz. This equipment will allow the analysis of fixations, saccades, pupillary dilation or and blink rate, during the LSPT. The ETS was only applied in the LSPT, as it contains visual stimuli while performing gaze orientation and control of attention, appearing as especially appropriate to analyze gaze patterns (53). In addition, the LSPT is longer in duration, which makes it possible to collect consistent eye activity data. Vansteenkiste et al. (54) demonstrated a correlation between LSPT performance and gaze patterns in young players, reinforcing that this type of test is suitable for analyzing oculomotor metrics. In contrast, the Y-SART is a simple task and it presents brief visual stimuli, so the use of an eye-tracker is not justified. Recent research has demonstrated that motor skills (e.g., sprinting, changing direction, reactive strength) are the main determinant in performance on the Y-SART and is also affected by sensory/perceptual processes to a smaller extent or indirectly (55). The data will be processed with open-source software provided by the manufacturer.

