#### Oculomotor parameters (ETS)

2.5.2

Oculomotor parameters will be monitored using the Pupil Pro Eye Tracking Headset (Pupil Labs GmbH, Germany) to assess neurophysiological changes associated with mental fatigue induced by the ST. The metrics analysed will include the number and average duration of fixations, the duration and average speed of saccades, pupil diameter, and blink rate, parameters widely recognized as sensitive indicators of cognitive load, attention regulation, and fatigue-related decline in vigilance (69–72). To minimize potential confounding influences, standardized task instructions, calibration procedures, controlled lighting conditions, and consistent testing environments will be implemented. Moreover, the within-subject pre-post design allows each participant to serve as their own control, thereby reducing the impact of inter-individual variability in visual strategies and perceptual tendencies.

In addition to descriptive characterisation, the study will include comparisons between the experimental and control groups in terms of these oculomotor parameters after the intervention phase. These comparisons will assess whether mental fatigue induced by the ST produces significant changes in visual-attentional dynamics compared to a cognitively neutral task. Specific attention will be given to variations in blink rate, pupil diameter, fixation duration, and saccade characteristics.

Within the experimental group, oculomotor parameters will be compared before and after the intervention to identify the direct impact of cognitive overload on visual attention and eye movement control. This intragroup analysis is crucial for understanding the dynamic response of the oculomotor system to cognitive stress.

In addition, correlational analyses will be performed between ETS data and behavioral performance on the LSPT and Y-SART to explore whether visual-attentional indicators predict motor performance under fatigue. A multimodal approach will also be employed to assess convergence between different markers of fatigue (ETS, EEG, and VAS), providing a comprehensive understanding of how different modalities reflect fatigue-related changes.

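### The protocol contradicts itself on which motor test and which phase use the eye tracker; followed literally, section 2.4 leaves the planned before-after gaze analyses without a baseline

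*Protocol article*

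**What the plan says.** **Which test.** Section 2.3 of the protocol article states that "The ETS was only applied in the LSPT, as it contains visual stimuli while performing gaze orientation and control of attention". It gives the reason for leaving out the other test: "the Y-SART is a simple task and it presents brief visual stimuli, so the use of an eye-tracker is not justified". The Introduction likewise places head-mounted eye tracking in the LSPT. Section 2.4, in the paragraph after Figure 3, says of Phase 5: "both motor tests are repeated, this time with continuous recording by the ETS".

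**Which time.** Section 2.4 opens the pre-test with "After collecting baseline data, participants will perform two motor tests as part of Phase 3 of the protocol". It goes on to describe the passes, the scoring, two cameras, the light-stimulus system and automatic timing. The eye tracker is not mentioned there and first enters the procedure at the Phase 5 repeat.

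**What the analysis needs.** Section 2.5.2 says that within the experimental group "oculomotor parameters will be compared before and after the intervention", and answers differences between people in visual strategy with the argument that "the within-subject pre-post design allows each participant to serve as their own control". Section 2.6 lists oculomotor parameters among the outcomes to be summarised by group and by pre and post. It also plans paired t-tests within each group and independent t-tests at each time point.

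**The concern.** There are two separate conflicts in the current text. Sections 2.3 and 2.4 disagree on whether the Y-SART is recorded. The procedure in section 2.4 and the analyses in sections 2.5.2 and 2.6 disagree on whether gaze is recorded before the intervention.

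The second matters more. Staff who work from section 2.4 would fit the tracker only for Phase 5. A gaze baseline that was not recorded before the 30-minute task cannot be recovered afterwards. The before-after gaze analysis, which section 2.5.2 treats as essential to its question, would then have no data on one side.

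There is also a side effect on performance. If the headset is worn at the second LSPT and Y-SART but not at the first, any effect of wearing it becomes part of the pre-post change in both scores.

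**Working it through.** The point disputes no figure in the plan, so the check is a comparison of the statements, followed by a short piece of algebra for the headset.

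**Step 1. The statements side by side.**

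| Place | Test recorded | Time recorded |
|---|---|---|
| Section 2.3 | LSPT only; Y-SART ruled out | no phase stated |
| Section 2.4, Phase 3 | tracker not mentioned | tracker not mentioned |
| Section 2.4, Phase 5 | both motor tests | at the repeat, worded as a change from the first time |
| Section 2.5.2 | not restated | before and after needed |
| Section 2.6 | not restated | pre and post needed |

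Rows 1 and 3 conflict on the test. Rows 2 and 3, read together, conflict with rows 4 and 5 on the time. No text shown states that gaze is recorded at the Phase 3 LSPT.

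**Step 2. The outcomes affected.** Section 2.5.2 names number and mean duration of fixations (2), duration and mean speed of saccades (2), pupil diameter (1) and blink rate (1): 2 + 2 + 1 + 1 = 6 metrics.

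**Step 3. What depends on a Phase 3 recording.**

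- Cannot be computed without it: the within-group before-after gaze comparison (2.5.2 and the paired t-tests in 2.6), the pre-test gaze summaries and pre-test group comparison (2.6), and the gaze part of the intra-subject multimodal analysis (2.5.6). The own-control argument in 2.5.2 falls with them.
- Can still be computed: the comparison of experimental and control groups on gaze, which 2.5.2 places after the intervention, and the correlations of the post-intervention fatigue rating (VAS) with gaze (2.5.4.2).

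A paired difference needs both members of the pair, so the first list fails at any sample size.

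**Step 4. The headset and the performance scores.** Suppose the headset is worn only in Phase 5. Write the mean pre-post change in an arm as P + H + F, with P the effect of repetition and time, H the effect of wearing the headset, and F the effect of the assigned task.

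- Experimental arm: P + H + F(Stroop)
- Control arm: P + H + F(reading)
- Difference between arms: F(Stroop) − F(reading)

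If H is additive and the same in both arms, it cancels in the randomised contrast. It does not cancel within one arm. The within-experimental-group comparison of LSPT and Y-SART, which section 2.5.3 uses to detect deterioration due to the Stroop task, would carry H. The protocol gives no information on the size or direction of H.

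**The case against.** The strongest objection is that the missing baseline is inferred from one phrase and from silence. Section 2.3 ties the tracker to the LSPT without limiting it to one phase. Sections 2.5.2 and 2.6 both imply recording at both times. Section 2.1 refers the reader to Figure 1 for the data collection moments; that figure was not available for this review and may mark the tracker in Phase 3. The article also condenses a fuller protocol. Loose wording in section 2.4 is therefore a live explanation. This stands, and it makes the lost baseline conditional. It does not remove the conflict over the Y-SART, which is explicit on both sides, and it does not make section 2.4 safe to follow as written.

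Two stronger readings are tempting and are not supported:

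- A reader might infer that the group comparison of gaze loses power. Section 2.5.2 already plans that comparison after the intervention, and baseline adjustment is not planned for gaze: ANCOVA appears in section 2.6 only for demographic and contextual covariates. The stated between-group test is the same with or without a Phase 3 recording.
- A reader might infer that the headset confounds the fatigue effect itself. Under the additive assumption in the working it does not; only the within-arm comparisons are exposed.

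**Conclusion.** The contradiction is certain; its consequence is conditional. The text disagrees on whether the Y-SART is recorded, and its procedure does not provide the pre-intervention gaze recording that its own analyses need.

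If section 2.4 is followed to the letter, the within-subject gaze analyses are lost for the whole trial and cannot be repaired later. The within-group performance comparisons would also mix the headset with time. The randomised between-group comparisons of gaze and performance survive, for performance on the assumption that a headset effect is additive and equal in the two arms.

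A reader might infer that the baseline is definitely missing. The document does not establish that, because sections 2.3, 2.5.2 and 2.6 fit recording at both times. The passages still have to be reconciled before the first session.

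**What to change.** Reconcile sections 2.3, 2.4 and 2.5.2 under one rule: the eye tracker is calibrated, worn and recorded during the LSPT in both Phase 3 and Phase 5, and is not worn for the Y-SART at either time. This follows section 2.3's own reason for leaving out the Y-SART and section 2.5.2's own analysis.

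In section 2.4, add the tracker to the Phase 3 LSPT description. In the Phase 5 sentence, remove the words that extend the recording to both tests and those that present it as new at the repeat. Check that Figure 1 shows the same schedule.

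The cost is a change of wording. If Phase 3 recording is not already intended, add one calibration and one recording per participant with equipment the study already uses.
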